
### Follow-up procedure

Follow up measurements of all outcome measurements will be recorded at eight weeks (on completion of trial) and at six months after randomisation into the trial by a member of the research team who shall remain blinded to group allocation throughout the study.

### Focus Groups

Qualitative exploration of individuals' perception of walking will also be examined by use of focus groups at the end of the intervention. Participants in group B will be invited to one of three to five groups, consisting of between 5 and 8 participants, to discuss their experiences, expectations and satisfaction with the walking programme. Each focus group will consist of a maximum of eight participants and will take place over a two-hour period. A 'clue and cue process', using a checklist of topics, will be used to ensure that the same basic areas are covered, but allowing any issues of importance to emerge. Sessions will be moderated by an experienced, independent focus group moderator who will have had no previous contact with study participants prior to the focus group meetings. Audio-tape recordings and field notes will be prepared by another member of the research team not involved in the running of the trial. Interviews will be transcribed, and interpretation, synthesis and data reduction undertaken independently by two members of the research team. Analysis will then be undertaken using qualitative research and data analysis software (N-VIVO [QDSR]). The findings will be presented to participants and therapists for their feedback and to help inform further research.

### Sample size

No formal sample size calculation will be carried out. As a feasibility study, we aim to recruit a total sample of 50 participants (Approximately 17 in Group A and 33 in Group B according to the 1:2 randomisation methods). This sample size reflects both a realistic target for the intervention period and one which we anticipate will provide sufficient information on the interventions to inform future studies. In particular, we are interested in gathering as much information as possible on any adverse events (including minor musculoskeletal injuries) associated with the walking intervention. Two reported adverse events in the walking group will represent an approximate incidence of 5%.

### Statistical analysis

As a feasibility study, significance tests will not be performed or reported for the primary or secondary outcomes. Treatment effects will be represented by point estimates and confidence intervals. The assessment of participant satisfaction will be tabulated, as will adherence levels and any recorded difficulties or adverse events experienced by the participants or therapists. This information will be used to modify the planned interventions to be used in the main RCT. The following criteria would suggest that a main trial is not feasible: no apparent change in the outcomes with confidence intervals that include large negative values, feedback from participants that they were unable to complete (or lack of adherence with) the walking programme and/or unable to use the pedometers; high levels of musculoskeletal injuries occurring.

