### Specific objectives are as follows

**i**. To assess recruitment and adherence rates in education and advice and education and advice plus walking programme groups.

**ii**. To determine the incidence of adverse events, including musculo-skeletal injuries, and level of overall satisfaction in both groups.

**iii**. To conduct a qualitative exploration of participants' experience of the walking plus education group.

**iv**. To make between and within group comparisons and estimate effect sizes for change in functional disability, PA levels, stage of change, fear-avoidance, self-efficacy, health-related quality of life, psychosocial beliefs, general health and participant satisfaction.

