### Identification of potential participants and screening procedures

In order to maximise recruitment and to ensure that the sample size is achieved, potential participants will be identified from a number of sources.

I) The Physiotherapy department at the Robinson Memorial Hospital, Ballymoney will serve as one recruitment source. Potential participants will be identified from the referral lists and sent a letter inviting them to take part in the research study. This letter will state clearly that the individual is under no obligation to take part in the study and that non-participation will not prevent them from still receiving a standard physiotherapy appointment after the 9-13 week waiting list. The 8 week intervention period of the study therefore fits within this timescale. Interested participants will contact the Physiotherapy department to arrange an initial appointment time. They will then be sent a confirmation letter and information sheet which will allow for a 'cooling off' period of approximately one week.

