### Treatment allocation

A statistician who will have no contact with the day to day running of the study shall carry out all aspects of preparation for group randomisation. A randomisation sequence will be generated using computer software with an allocation ratio of 1:2. This is order to ensure more information can be gathered on the walking intervention group (Group B). This is relevant since we wish to gather as much detail as possible regarding adverse events or other side effects and will enable us to learn more about the type and level of training required for this intervention in a fully powered trial. Blank cards will be printed with Group A (Education and advice) or Group B (Education and advice plus a structured walking programme). These cards will be placed inside sequentially numbered opaque sealed envelopes. Following baseline assessment, these envelopes will be used to assign participants in sequence to one of the two treatment groups (Group A or Group B). Participants will therefore be randomised under strict double-blind conditions.

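### Adherence and adverse events, which feed the judgement on whether a main trial is feasible, are to be tabulated without intervals, and objective (iv) promises a change in satisfaction that is measured only once

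*Protocol article*

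**What the plan says.** The Statistical analysis section of the protocol article sets two forms of presentation, one after the other.

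- For outcomes: "Treatment effects will be represented by point estimates and confidence intervals". No significance tests are planned.
- Participant satisfaction "will be tabulated, as will adherence levels and any recorded difficulties or adverse events". No interval is mentioned for these items. The information is to be used to modify the interventions for the main trial.

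The section then lists what would count against a main trial: no apparent outcome change with intervals reaching large negative values; participant feedback of inability to complete the programme, lack of adherence, or inability to use the pedometer; and high levels of musculoskeletal injury.

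Objective (i) is: "To assess recruitment and adherence rates in education and advice and education and advice plus walking programme groups". Objective (ii) covers adverse events and overall satisfaction. Objective (iv) promises between- and within-group comparisons and effect sizes for change in a list of outcomes that ends "health-related quality of life, psychosocial beliefs, general health and participant satisfaction".

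The Sample size section states: "we aim to recruit a total sample of 50 participants", split as "Approximately 17 in Group A and 33 in Group B according to the 1:2 randomisation methods". It makes no formal calculation, and equates two adverse events in the walking group with an incidence of roughly 5%.

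The text on Group B under Treatment protocols defines compliance as each participant's self-reported steps as a percentage of target. The end of the Outcome Measures section says the satisfaction questionnaire is administered on completion of the trial.

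**The concern.** In a feasibility study, adherence and safety are main results. This plan gives intervals to the treatment effects and a plainer presentation to adherence and adverse events, although both inform the judgement on a main trial. The Sample size section sets no precision target, so an interval is the natural guide to what a rate from about 33 people can support. Without one, a favourable or unfavourable table could be given more weight than the numbers bear. The article's own conversion of two events into a single percentage, with no range, shows how this can happen.

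Satisfaction is a separate problem of consistency. Objective (iv) asks for an effect size for change, the measurement schedule gives a single reading, and the analysis section only tabulates it. The three statements cannot all be carried out.

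**Working it through.** **Inputs.** Total sample 50, and randomisation "with an allocation ratio of 1:2" (Sample size; Treatment allocation). The article states no confidence level, so 95% is assumed throughout. All adherence and satisfaction counts and all SDs below are assumed for illustration. Only the two adverse events come from the article.

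**Group sizes.** 50 × 1/3 = 16.7 and 50 × 2/3 = 33.3, which reproduces the stated 17 and 33.

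**The stated incidence.** 2/33 = 6.1%. A figure of 5% would need 2/40, so the stated value is loose. The larger matter is its precision.

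**Exact (Clopper-Pearson) intervals.** For x of n, the lower limit is the 2.5% quantile of Beta(x, n − x + 1) and the upper limit is the 97.5% quantile of Beta(x + 1, n − x). If x = 0, the lower limit is 0. Each event is taken to fall in a different participant.

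| Quantity | x/n | Estimate | 95% interval |
|---|---|---|---|
| Walkers with an event | 0/33 | 0% | 0% to 10.6% |
| | 2/33 | 6.1% | 0.7% to 20.2% |
| | 5/33 | 15.2% | 5.1% to 31.9% |
| Controls with an event | 2/17 | 11.8% | 1.5% to 36.4% |
| Walkers adherent (if dichotomised) | 17/33 | 52% | 34% to 69% |
| | 23/33 | 70% | 51% to 84% |
| | 30/33 | 91% | 76% to 98% |

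**Adherence as the article records it.** Compliance is a percentage of target for each participant, so a mean may be the better summary. The half-width is t(0.975, 32) × SD/√33:

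- SD 10 points: 3.5 points
- SD 20 points: 7.1 points
- SD 30 points: 10.6 points

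A mean is therefore better determined than a yes/no rate. For comparison, the normal approximation 1.96 × √(p(1 − p)/33) gives 17 points at p = 50% and 10 points at p = 90%.

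**Satisfaction.** Set the three places side by side. Objective (iv) requires change and a within-group comparison. The Outcome Measures section schedules the questionnaire on completion, with no baseline. The Statistical analysis section tabulates it. With no baseline value, neither a change from baseline nor a within-group comparison can be computed. A between-group difference in level can be. With assumed counts of 28/33 and 12/17 satisfied, the difference is 0.848 − 0.706 = 0.143. The Wald standard error is √(0.848 × 0.152/33 + 0.706 × 0.294/17) = 0.127, so the 95% interval is about −11 to +39 points.

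**The case against.** The strongest reply is that tabulating does not rule out an interval, that table layout is usually left to an analysis plan, and that readers can compute intervals from the stated denominators. Part of this stands: the article does not forbid intervals. But it is not silent either. It specifies intervals for one class of result and a different presentation for the other, and objective (i) falls in the second class.

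A reader might infer more than the text supports:

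- *That the main-trial decision rests only on tabulated items.* It does not. Outcome change is one of the listed grounds and is to be judged with confidence intervals.
- *That satisfaction drives the decision.* It is not among the listed grounds.
- *That completion and pedometer use are also merely tabulated rates.* They are not named among the tabulated items. They enter as participant feedback and concern Group B only.
- *That results will be pooled over recruitment sources.* The article says several sources are used: "In order to maximise recruitment and to ensure that the sample size is achieved, potential participants will be identified from a number of sources". It does not say how tables will treat source.
- *That readers will take the figures as exact, or that the main trial must be planned from the unfavourable limit.* The first is a prediction about readers and the second a preference. Neither is an error in the text.
- *That estimation without tests is a fault.* It suits a feasibility study.

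It is also fair to object that a proportion such as 23/33 needs an adherent/non-adherent cut-off, which the article does not define. That is why the mean percentage of target is offered as an alternative.

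On satisfaction, it could be said that the word change was simply carried over a long list. That is probably so, but the objective still cannot be met as written.

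**Conclusion.** The point holds in limited form. The article plans intervals for treatment effects but only tabulation for adherence and adverse events. Adherence is a named objective, and lack of adherence and high injury levels are two of the stated grounds against a main trial. At the planned size the imprecision is large enough to affect how those grounds are read: two walkers with an event are compatible with an incidence from below 1% to about 20%, and an assumed 70% adherence rate with anything from about half to 84%. These figures assume the full 33 walkers, a 95% level and one event per affected participant. The adherence counts are illustrative.

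The inconsistency over satisfaction is definite and needs no assumption beyond the stated single administration. It is a smaller matter, because satisfaction does not enter the feasibility criteria.

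**What to change.** In Statistical analysis:

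- Report walking-group adherence as the mean percentage of step target with a 95% t or bootstrap interval. If it is dichotomised, define the cut-off and give n/N with an exact interval.
- Report musculoskeletal injuries and other adverse events per group as participants affected, n/N, with exact 95% intervals.
- Where completion and pedometer use are counted, give n/N with an interval for Group B only.
- State that the non-feasibility criteria will be read with these intervals in view.

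In Sample size, replace the approximate 5% with 2/33 = 6.1% (0.7% to 20.2%).

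Reconcile objective (iv) with the Outcome Measures and Statistical analysis sections: remove satisfaction from the outcomes assessed for change and within group, and report its between-group difference in level with a 95% interval.

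The cost is a few sentences and some table columns, with no new data. The feasibility figures will look less certain, which reflects what 50 participants can show.

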### Adverse event recording

Any adverse events will be reported using a standard proforma.

### Service user involvement

Two service users will sit on the research team panel during the developmental and running stages of the study.

### Training requirements

Both service users will attend two separate training sessions at the research centre to familiarise themselves with the study procedures. In addition, all physiotherapists involved in delivering the interventions will receive a standardised period of training prior to commencement of the study.

## Discussion

This paper describes the rationale and design of a study which will test the feasibility of using a structured, pedometer-driven walking programme in participants with CLBP. This study will be to provide important practical information on pedometer prescription for physiotherapists and people with CLBP. The longer-term objective is to provide the ground work necessary for a main trial to establish whether the use of such initiatives are more effective than simply giving advice to be more active.
